### Intervention

The study’s framework (Fig. 1) describes the links between the components of the intervention. The training component is partly adapted from Robson et al.’s theory of how training can be effective in leading to improved health outcomes [20]. This considers worker and manager training as part of the wider workplace environment, where its effectiveness is modulated by other individual and organizational factors. In accordance with that framework, the intervention package will comprise four components:
Initial training for all workers and managers on occupational health and safetyFollow-up refresher sessions every 3 monthsFormation of workplace committees (including worker representatives) to draw up, agree and promote a health and safety plan that includes wet mopping, safe disposal of cotton dust, and the use of simple face-masks, as well as further publicity about the risks from cotton dustProvision of adequate supplies of face-masks to support the health and safety plan

**Fig. 1 Fig1:**
[figure not shown]
MultiTex RCT – Conceptual framework of the trial

An initial series of training sessions will be conducted in the intervention arm to explain the health hazards of cotton dust and appropriate preventive measures. These sessions will be based on ‘adult learning theory’ [18, 23], and will be delivered separately to the workers and managerial staff. To reinforce the content, regular refresher sessions will then be conducted every 3 months for the workers and every 6 months for the managers.

At each mill in the intervention arm, an Environmental and Occupational Health (EOH) plan will be developed with management and worker representatives, covering steps to be taken in implementing the intervention package. As part of the plan, wet mopping and safe disposal of cotton dust (such as keeping it in closed containers and avoiding direct contact of workers with trash) will be promoted. Guidance will be provided to ensure that any available local exhaust ventilation system is functioning satisfactorily. In addition, better personal and workplace hygiene will be promoted among the workforce. Implementation of the EOH plan will be documented as part of the trial’s fidelity assessment.

Smooth delivery of the EOH plan will be assisted by formation of a “MultiTex” Committee at each mill in the intervention arm. This Committee, which will include workers’ representatives, will be responsible for quality assurance and addressing day-to-day challenges.

In addition to training sessions, workers will be provided with simple disposable face-masks, commonly known as “surgical face-masks,” for use during working hours. MultiTex Committee members will be responsible for keeping a log of the number of face-masks distributed per shift and the number of workers who actually use them.

We do not intend to provide any intervention to the mills in the control group during the course of the main study. However on conclusion of the study, and if the trial is successful in achieving the desired outcomes, those mills will be provided with the same intervention. This will comprise all components of the intervention package except for the refresher sessions.

### Measurements and their frequencies

To assess the impact of the intervention, surveys will be carried out across all mills at baseline (i.e., before the intervention is implemented), and then at follow-up 3, 12 and 18 months later (Figs. 2, 3 and 4, and Additional file 1). The surveys will include detailed interviews using a questionnaire, and spirometry for each worker. In addition, personal dust exposures, measured with Institute of Occupational Medicine (IOM) samplers, will be recorded for selected sub-samples of participants.

**Fig. 2 Fig2:**
[figure not shown]
Mill selection

**Fig. 3 Fig3:**
[figure not shown]
Intervention and measurement schedule; *AKU* Aga Khan University, *KAP* knowledge, attitude and practices

**Fig. 4 Fig4:**
[figure not shown]
Standard Protocol Items: Recommendations for Interventional Trials (SPIRIT) Figure. Schedule of enrollment, interventions and assessments in the MultiTex RCT. *KAP* knowledge, attitude and practices

#### Interviews

To assess respiratory symptoms we will use a translated version of the Medical Research Council (MRC), UK respiratory questionnaire [24]. Questions concerning byssinosis will be taken from the World Health Organization (WHO) respiratory questionnaire from technical report series 684 [25]. To assess knowledge, attitudes and practices (KAP) among textile workers and managers we will use a structured questionnaire which was developed by the authors as part of previous research on textile workers. The study questionnaires will be pretested and delivered by trained data collectors in the field. The total time required for the questionnaires will be approximately 20 min.

#### Spirometry and anthropometric measurements

We will use the ndd (EasyOne) spirometer to measure lung function, following established guidelines [26]. Forced expiratory volume in the first second (FEV_1_), forced vital capacity (FVC) and the FEV_1_/FVC ratio will be recorded. Pre- and post-bronchodilator spirometry will be conducted at least 1 h after the worker has started a shift (i.e., after he has been exposed to cotton dust that day). We will note the time of the day when spirometry is carried out, as well as the interval since start of the shift, and the number of consecutive days that have been worked leading up to the measurement. Every effort will be made to undertake spirometry at each follow-up on the same working day and during the same shift as at baseline. For a sub-sample of 100 randomly selected workers in the highly exposed job categories (helpers/cleaners and machine operators), pre- and post-shift spirometry will additionally be performed, to gauge cross-shift changes in lung function. We will record height in centimeters using a stadiometer, and weight in kilograms.

#### Cotton-dust exposures

We will use IOM sampling heads with Casella Apex2 pumps for personal monitoring of dust exposures, measuring the inhalable fraction of particulate matter (PM < 100 μm) over an 8-h shift. Pre- and post-sampling airflow and sampling time will be recorded, as well as temperature and humidity readings. Each individual’s average PM exposure concentration will be calculated from the difference in filter weights and sampled air volume. Individual data will then be combined to derive mean exposures for combinations of job and section at each mill. Where possible, the same workers will be monitored at follow-up as at baseline, but those who cannot be re-contacted will be replaced by others with similar job tasks. Dust sampling will be done at all the textile mills across the intervention and control arms at baseline and will be repeated at 3, 12 and 18 months after intervention. In addition to personal sampling, area sampling will be carried out in the spinning and weaving sections of each mill using a Dylos DC 1700 particle counter to measure the average concentration of dust (particle size > 0.5 or > 0.25 μm) over an 8-h shift. The particle counters will be placed at fixed sites in the centres of work stations in the spinning and weaving sections, at approximately 1.5 m height, and away from the ventilation outlets or fans. Side-by-side gravimetric and Dylos measurements will be made for a small number of sites to provide a calibration factor for the Dylos particle concentration in relation to cotton dust.

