### Recruitment and randomization

In Pakistan, no official sampling frame of textile mills is available but several business and textile associations represent the country’s textile mills and from them we will acquire a list of industrial plants in Karachi. To be eligible, textile mills will need to: (1) be from the formal sector and registered with business associations and the Government Labor Department; (2) have either spinning or weaving sections, or both; (3) employ at least 50 eligible workers in their spinning and weaving sections; (4) have a workforce in which at least 75% of staff have been employed for 12 months or longer; (5) have a management willing to participate in the planning and implementation of the study and (6) have no plans to introduce major improvements over the next 2 years.

Eligible workers at each mill will be identified by the Human Resources Department. We will include male textile workers aged ≥ 18 years who are employed in the bale-opening, blowing, carding, spinning, twisting, winding, warping, weaving or waste recycling sections. In Pakistan, women very rarely work in these sections and we will not include them. Those who do not give consent will be excluded. We will also exclude workers from the wet-processing areas (dyeing or bleaching), stitching and packaging sections, as well as support or administrative staff. At each mill, personal air sampling will be done on five purposively selected workers (100–150 in all) representing the range of sections and jobs. For this purpose, the latter will be categorized into one of four groups: (1) helpers, cleaners and doffers; (2) machine operators; (3) jobbers and fitters and (4) masters, in-charge or supervisors.

We will purposively select 28 textile mills and assign them equally to the intervention or the control arm by stratified randomization. Stratification will be according to the total number of employees at the mill (≤ 250/> 250) and occupational health and safety measures in place at baseline (as assessed by a walk-through survey and categorized as good or poor). Within strata, allocation to intervention or control will be through random numbers generated at Imperial College London and shared with the research team in Pakistan. Blinding of mill staff will not be possible but we will “blind” the data collection team including the technicians measuring dust levels, and the laboratory personnel involved in weighing filters for gravimetric analysis.

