### Statistical power

Based on previous occupational trials, we assumed that the intra-class correlation coefficients for the outcome measures were 0.02 [29, 30].

For cotton-dust levels: assuming the level of significance at 5%, power 80% and a 15% or 0.65 mg/m^3^ difference in mean PM levels in the intervention arm compared to the control arm (expected mean dust level in control arm: 0.6 with a standard deviation of 2.5); the sample size required without clustering is 233/arm. The variance inflation factor is:
$$ \left[1+\left(50-1\right)\ast 0.02\right)\Big]=1.98, $$

so the sample size is inflated to 461, which rounds up to 10 groups of 50 in each arm – which increases to 10 groups of 61 in each arm after inflating for losses (* 1.05 * 1.05 * 1.1 = * 1.212).

For respiratory symptoms: the trial is powered to detect a difference of 10% in the proportion of workers reporting respiratory symptoms between the intervention and control arms. Assuming a level of significance at 5%, power 80%, the proportion of workers having respiratory symptoms at the baseline as 40%; without clustering we would require 354/arm. With clustering, the new sample size is 701/arm which – in groups of 50 – means 14 groups of 50 in each arm of the study. Inflating these numbers for losses gives 14 groups of 61.

For lung function: assuming level of significance at 5%, power 80%, 5% or a 150-ml difference in mean FEV_1_ (standard deviation 31) in the intervention arm compared to the control arm (expected mean FEV_1_ in control arm: 3279 ml, standard deviation 690); the requirement without clustering would be 333 per arm, which inflates to 660 with clustering, which again leads to 14 groups of 50 in each arm and this again inflates to 14 groups of 61 after inflating for losses.

Based on the above calculation, we intend to recruit 854 workers from 14 clusters in each arm, a total of 1708 participants in 28 clusters.

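### Five personal dust samples per mill cannot support the job-by-section mean exposures planned within each mill; at multi-section mills some combinations stay empty and most others hold one reading

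*Protocol article*

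**What the plan says.** All references are to the protocol article.

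- **Aggregation rule** (Cotton-dust exposures): "Individual data will then be combined to derive mean exposures for combinations of job and section at each mill".
- **Number sampled** (Recruitment and randomization): "At each mill, personal air sampling will be done on five purposively selected workers (100–150 in all) representing the range of sections and jobs". For jobs, "the latter will be categorized into one of four groups": helpers, cleaners and doffers; machine operators; jobbers and fitters; and supervisory grades.
- **Sections in scope** (same section): eligible workers are those "employed in the bale-opening, blowing, carding, spinning, twisting, winding, warping, weaving or waste recycling sections", which is nine named sections. Mills qualify if they "have either spinning or weaving sections, or both", so not every mill will have all nine.
- **Follow-up** (Cotton-dust exposures): sampling is repeated at 3, 12 and 18 months, on the same workers where possible and otherwise on replacements doing similar work. Fixed-site particle counters also measure dust in the spinning and weaving sections, and are calibrated against gravimetric samples at a few sites.
- **Use of the data**: personal dust and its change from baseline form the first primary outcome (Study outcomes). Statistical analysis plans GEE models for change in dust, and Pearson correlations of dust with FEV1, FVC and their ratio.
- **Size** (Statistical power): "we intend to recruit 854 workers from 14 clusters in each arm, a total of 1708 participants in 28 clusters".

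**The concern.** The aggregation rule and the sampling plan do not fit together. The rule works at the level of job by section within a mill, while the sampling plan supplies five readings to the whole mill. Because the five workers are meant to span the range of sections and jobs, the expected result is one reading in each combination reached and none in the rest.

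Two things are at stake. First, a combination with no sample has no mean, and the article gives no way to fill it. Second, a combination with one sample has a mean equal to one man's dust on one shift. If that value is assigned to his colleagues, they all inherit that day's deviation. This would tend to weaken any association between dust and lung function. The size of the effect cannot be computed, because the article gives no split of dust variance into between-worker and day-to-day parts.

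**Working it through.** **Inputs.** Five samples per mill per survey, four job groups and nine named sections (Recruitment and randomization); 28 mills and 1708 workers (Statistical power); four survey rounds (Measurements and their frequencies). The number of sections at any one mill, S, is not given, so it is varied below.

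**The plan's own figure.** 5 × 28 = 140, which lies inside the stated 100–150 in all. Per arm this is 5 × 14 = 70. The share of workers measured directly is 140 / 1708 = 8.2%; per mill, 854 / 14 = 61 workers and 5 / 61 = 8.2%.

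**Combinations that can be filled.** With all four job groups present there are 4 × S combinations, and five samples fill at most five.

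| Sections S | Combinations 4 × S | Most that can be filled | Fewest left empty |
|---|---|---|---|
| 1 | 4 | 4 (100%) | 0 |
| 2 | 8 | 5 (62.5%) | 3 |
| 3 | 12 | 5 (42%) | 7 |
| 5 | 20 | 5 (25%) | 15 |
| 9 | 36 | 5 (14%) | 31 |

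**Readings per filled combination.** If the five samples fall in five combinations, all five means are single readings. If they fall in four, three are single readings; this includes the one-section mill with every job group covered. At most two combinations can hold two or more readings (2 + 2 + 1).

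**Later surveys.** Four rounds give at most 4 × 5 = 20 samples per mill. They largely repeat the same five combinations, because the same workers or job-matched replacements are sampled. Pooling rounds within a mill would also mix baseline with post-intervention exposure.

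**Area sampling.** The fixed counters give a value by section, not by job, so they cannot fill a job-by-section combination.

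**Workers in a sampled combination.** This needs a job mix, which the article does not give. The mixes below are assumptions, with workers spread equally over sections.

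| Assumed job mix and choice of five | S=2 | S=3 | S=5 | S=9 |
|---|---|---|---|---|
| Even mix (25% each) | 62.5% | 42% | 25% | 14% |
| 35/50/10/5, five most populated combinations | 90% | 73% | 50% | 28% |
| 35/50/10/5, one per job group plus one more in the largest | 75% | 50% | 30% | 17% |

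For example, with the 35/50/10/5 mix and S=2, the five largest combinations hold 25 + 25 + 17.5 + 17.5 + 5 = 90% of workers. With one section and all four groups sampled, coverage is 100%.

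**The case against.** The strongest reply is that the sentence promises less than it seems to. It speaks of combinations of job and section, not of every combination, and does not say that a mean is assigned to each worker. Measurements and their frequencies limits personal dust to sub-samples. This stands in part. If only sampled combinations are meant, the step can be carried out, but most of its means are then individual readings under another name.

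A second reply is that the nine-section case is extreme. Many mills may have fewer sections, and the article often uses section in a broad sense for spinning and weaving. On that reading a single-type mill has four combinations, which five samples can cover, and a combined mill has eight. This is fair, and is why the result is shown over a range of S. The mismatch still holds from two sections upwards.

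A third reply is that pooling and prediction belong in an analysis plan, which is not shown. Their detail does. The point here is only that a stated rule does not match the stated sampling.

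Three stronger readings are tempting, and the article does not support them:

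- *Most workers end up without a usable dust value, or are dropped.* No assignment or exclusion rule is stated, and coverage runs from about 14% to 100% under the assumptions above.
- *The primary dust comparison fails.* Each sampled worker's own concentration is calculated, and the GEE models can use it. Dust by section has the area counters, and the symptom and FEV1 comparisons need no dust value.
- *Pooled data are clearly ample for every combination.* 140 / 36 = 3.9 samples per combination per survey and 4 × 3.9 = 15.6 over four surveys look comfortable, but they assume even spread and count repeat readings as new ones.

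**Conclusion.** The point holds in limited form. At any mill with two or more sections and all four job groups, five samples leave at least 3 of 8 combinations empty with two sections, 7 of 12 with three and 31 of 36 with nine. Most of the filled ones rest on one shift reading. Repeat surveys and area sampling do not repair this.

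The consequence is confined to analyses that use the within-mill means. The clearest candidate is the set of correlations between dust and lung function, and only if values are assigned to unsampled workers; that use is an inference. The number of workers affected is unknown, because it depends on sections per mill and job mix. The correction is worth making before exposure data are analysed, but it does not call the randomized comparisons into question.

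**What to change.** Replace the within-mill job-by-section means with exposures estimated by pooling across mills. One suitable form is a mixed model of log dust with additive fixed effects for job group, section, survey and arm-by-survey, and random effects for mill and worker. Use its predictions for combinations not sampled, and state that this is done. Compare the arms on the individual readings. Simpler pooling, by job group or by section across mills, would also resolve the mismatch.

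Job group and section together need 3 + 8 = 11 contrasts if all nine sections occur, against up to 36 separate means at each mill. The worker effect is needed because the same men are re-monitored; the up to 4 × 140 = 560 readings must not be treated as independent.

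The cost is analysis wording only, with no new sampling. The price is the assumption that job and section effects are similar across mills apart from the mill effect, and each section must have been sampled at some mill. Keeping the within-mill rule would instead take at least 4 × S samples per mill per survey for a single reading in each combination: 8 with two sections, 12 with three and 36 with nine, and twice that for two readings.

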**Methods/design:**

We will conduct a cluster-randomized controlled trial at 28 textile mills in Karachi. The intervention will comprise: training in occupational health for all workers and managers reinforced by regular refresher sessions; the formation of workplace committees to draw up, agree and promote a health and safety plan that includes wet mopping, safe disposal of cotton dust, and the use of simple face-masks, as well as further publicity about the risks from cotton dust; and provision of adequate supplies of face-masks to support the health and safety plan. Participating mills will be randomized to intervention and control arms following a baseline survey. The impact of the intervention will be determined through follow-up surveys conducted at 3, 12 and 18 months. Data collection in the surveys will include spirometry, questionnaire-based interviews and cotton-dust measurements.

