### Study outcomes

The primary outcomes of the trial at 18 months post intervention, will be: (1) personal dust exposure levels (in mg/m^3^), and their change from baseline, in the intervention as compared with the control arm; (2) dust levels in different sections of the mill (in mg/m^3^), and their changes from baseline, in the intervention as compared with the control arm; (3) changes from baseline in the prevalence of respiratory symptoms, in the intervention as compared with the control arm (a composite variable will be used for presence of one or more respiratory symptoms including; cough, sputum, wheeze, shortness of breath and chest tightness) and (4) changes in FEV_1_ from baseline to follow-up, in the intervention as compared with the control arm.

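### Replacement dust-sampling workers are chosen after allocation by a non-random rule at unblinded mills, which leaves personal dust (primary outcome 1) open to selection that differs by arm

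*Protocol article*

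**What the plan says.** All references are to the protocol article.

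- **Outcome.** Study outcomes lists as the first primary outcome, at 18 months, "personal dust exposure levels (in mg/m^3^), and their change from baseline, in the intervention as compared with the control arm".
- **Who is sampled.** Recruitment and randomization states that at each mill "personal air sampling will be done on five purposively selected workers (100–150 in all) representing the range of sections and jobs". The jobs are sorted into four groups.
- **Replacement.** Cotton-dust exposures says that the baseline workers are monitored again where possible, but "those who cannot be re-contacted will be replaced by others with similar job tasks". Sampling is repeated at 3, 12 and 18 months.
- **Timing of allocation.** According to the Abstract, "Participating mills will be randomized to intervention and control arms following a baseline survey".
- **Blinding.** Recruitment and randomization accepts that "Blinding of mill staff will not be possible". It intends to blind the "data collection team including the technicians measuring dust levels, and the laboratory personnel involved in weighing filters for gravimetric analysis".
- **Access to workers.** The same section says: "Eligible workers at each mill will be identified by the Human Resources Department".
- **Averaging.** Cotton-dust exposures combines the individual results into means for each job-and-section combination within a mill.
- **Turnover.** The Discussion describes labour turnover as generally high and notes that workers also move between sections.

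**The concern.** The five workers chosen at baseline are picked by judgement, but before any mill knows its arm, so that choice cannot differ systematically between arms. Replacements are different. They enter after allocation, and the only stated criterion is that the work is comparable. The rule includes no random draw and no list fixed in advance, and it does not require the same section or shift.

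Deliberate manipulation is not needed for this to matter. It is enough that the workers who are put forward, or are easiest to reach, differ between arms. In an intervention mill they might be those most engaged with the dust-control plan. A difference in measured dust that arises this way looks the same as a treatment effect. Allowing for clustering in the GEE model does not correct it, and neither does analysing mills by assigned arm.

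The article is stricter elsewhere. Under Spirometry and anthropometric measurements, the cross-shift sub-sample of 100 workers is drawn at random, and repeat spirometry is to match the baseline working day and shift as far as possible. A primary outcome therefore has a looser selection rule than a supplementary measurement.

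**Working it through.** **1. The plan's own dust figures (Statistical power).** Inputs: difference 0.65 mg/m³, SD 2.5, 5% significance (taken as two-sided), 80% power, intra-class correlation 0.02.
- Per arm without clustering: 2 × (1.96 + 0.84)² × 2.5² / 0.65², which rounds up to 233, as stated.
- Variance inflation: 1 + 49 × 0.02 = 1.98, and 233 × 1.98 = 461, as stated.
- Losses: 50 × 1.05 × 1.05 × 1.1 = 60.6, rounded to 61, as stated.

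These figures reproduce, but they do not measure the present risk.

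**2. The dust sub-sample.** 28 mills × 5 workers = 140, within the stated 100–150, so 70 per arm.

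**3. How many replacements to expect.** The article gives no rate for the dust workers. Its general loss allowance is a factor of 1.212, which corresponds to a lost share of 1 − 1/1.212 = 17.5%. Applied to the dust workers (an assumption), 70 × 0.175 = 12.3, or about 12 replaced per arm.

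**4. How far averaging protects.** Four job groups across only two sections already give 8 cells, more than the five workers sampled. Many filled cells will then hold one worker, and a replacement's reading becomes the cell mean. Averaging limits selection between cells but not within a cell.

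**5. Form of the bias.** Bias in the arm difference = share replaced × net between-arm shift in replacements' exposure caused by selection. The shift is unknown. Illustrations at a 17.5% share:
- shift 0: bias 0;
- shift 0.25 SD (0.25 × 2.5 = 0.625 mg/m³): 0.175 × 0.625 = 0.11 mg/m³, or 17% of the 0.65 target;
- shift 0.5 SD (1.25 mg/m³): 0.175 × 1.25 = 0.22 mg/m³, or 34% of the target.

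Over a wider assumed range (10% to 50% replaced, same non-zero shifts), the bias runs from 0.1 × 0.625 = 0.06 to 0.5 × 1.25 = 0.63 mg/m³, or 10% to 96% of the target. With five per mill the design effect is 1 + 4 × 0.02 = 1.08. The standard error of the arm difference at a single survey is 2.5 × √(2 × 1.08/70) = 0.44 mg/m³. The nominal 5% type I error would then become about 5.2% to 30%.

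**6. Limit of these illustrations.** Statistical power gives a control mean of 0.6 mg/m³, yet equates 0.65 mg/m³ with 15%, which implies a mean of 0.65/0.15 = 4.3. If the mean is 0.6, replacements in one arm cannot average 0.625 or 1.25 mg/m³ below it. Step 5 shows how the bias scales and is not an estimate of its size.

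**The case against.** The strongest reply has four parts.

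**Omitted detail.** Who draws a replacement, and from which list, is field-manual material that an article may leave to the full protocol. This holds for the identity of the selector, and no fault is found there. But the article does state a rule for choosing replacements, and that rule rests on judgement. An analysis plan cannot undo a selection made in the field.

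**Existing safeguards.** The data collectors and dust technicians are to be blinded, and results are averaged by job and section. The fixed-site area sampling behind primary outcome 2 does not depend on which workers are chosen, so it offers a check. All three are real. None removes the risk: blinding the technicians does not blind the mill, a cell may hold one worker, and outcome 2 is a separate outcome. The sensitivity analyses under Statistical analysis concern losses to follow-up and do not mention replacements.

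**Motive in both arms.** Ethical considerations presents dust monitoring as a compliance benefit to mills generally, so control mills may also want to look clean. If selection is equal in both arms, the bias is zero. This is why the point is about exposure to bias and does not assert that bias will occur.

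**Replacement is legitimate.** In a cluster trial of a mill-level exposure, replacing workers is not invalid in itself. Agreed. The weakness is only the unstructured choice after allocation.

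A reader might also infer that mill staff pick the replacements. The article does not say so; it says only that Human Resources identifies eligible workers. Nor can one conclude that a worker from a cleaner section would simply be substituted, because such a worker would fall into a different job-and-section cell.

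**Conclusion.** The point stands as a weakness in design that should be corrected. Replacements for a primary outcome are chosen after allocation, by a non-random rule, at mills whose staff are unblinded, so the outcome is open to selection that differs by arm. The stated safeguards reduce this but do not remove it.

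The documents support a scale for how many workers are affected, about 12 of 70 per arm, if the plan's 17.5% loss allowance applies to the dust workers. They do not support a figure for the bias, which may be zero.

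Two stronger readings should be resisted. A reader might take the eligibility criterion that at least 75% of staff have 12 months' service as a 25% yearly turnover, and so put replacements at about 25 of 70 (70 × (1 − 0.75^1.5) = 24.5). That criterion is a tenure threshold at entry, not a turnover rate. A reader might also assume that replacements are 1 mg/m³ less exposed and report a bias of 27% to 54% of the target. That gap has no source in the article and exceeds the stated control mean of 0.6.

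**What to change.** - **Before randomization**, the research team draws a randomly ordered reserve list at each mill from the enrolled baseline workers, for each sampled worker's job group and section, and for the same shift where possible.
- **At each follow-up**, blinded staff take replacements strictly in list order and log the reason for each replacement and for each name passed over.
- **If a list runs out**, the team draws at random within the same job-by-section cell.
- **In reporting**, give the number of replacements by arm and survey. Add a sensitivity analysis restricted to workers sampled at both baseline and 18 months. That analysis is a complement only, since those who stay may themselves differ by arm.

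The purposive choice of the five baseline workers need not change.

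The cost is one random ordering per mill from workers already enrolled, a log entry per replacement and one extra analysis. No additional air samples are needed. The downside is slightly less flexibility in the field when the next listed worker is not on shift.
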